#### Trial assessments

•Yale-Brown Obsessive–Compulsive Scale (Y-BOCS)

•Yale-Brown Obsessive–Compulsive Challenge Scale (Y-BOCCS Challenge)

•Clinical Global Impressions Scale (CGIS)

•Neurocognitive tests: CANTAB (stop signal reaction time test, intra-extradimensional set shift), Prisoner’s Dilemma test (cooperation test), Fabulous Fruit game (habit learning test—only to be conducted with patients who have been screened for eligibility in person prior to COVID outbreak in March 2020, and familiarised with the process prior to attending the research site for stimulation).

•Adverse Events Questionnaire

#### Long-term follow-up assessments

Patients will be followed up 7, 14 (via telephone) and 28 days (in clinic at their next stimulation cycle and in clinic or via telephone at the last study follow-up planned 28 days after the final stimulation) after their participation in the study, using the Y-BOCS, Y-BOCCS challenge, MÅDRS, SDS and the CGIS by the RA. Any reported adverse events will be followed up by the clinician by phone; if deemed necessary, the patient may be asked to come back to the clinic.

#### Qualitative assessments

Patients will have the option to take part in one-to-one interviews conducted by the RA at two time points in the study: the first, prior to the first visit, and the second, once the patient has completed all three arms of the study. A semi-structured topic guide informed by existing literature will be developed following consultation with PPI representatives. This will ensure that elements of the lived experience and illness perceptions that are of importance to this patient group are captured by this research.

Should patients opt to discontinue the study at any point after providing consent, they will be offered an exit interview to discuss their experiences and motives for discontinuation with the RA.

All research staff (across both sites) will also be invited to be interviewed by the RA (based at HPFT) concerning their experience of working on the study and specifically their thoughts around the feasibility of a full-scale tDCS trial.

### Trial involvement

Patients will be asked not to alter their average intake of coffee and avoid alcohol the day before tDCS. They will be also asked not to drive after receiving the intervention; therefore, reasonable travel costs will be reimbursed if they have made relative arrangements or a taxi will be booked and paid for. This will be explained to potential participants in the information sheet. There is no financial reimbursement associated with the time commitment to the study.

#### First visit (Day 1)

•Patients will be consented then randomised by a clinician who will later deliver the intervention. As patients will be unable to drive after receiving the stimulation, the clinician will check that suitable transport arrangements are in place.

•Pregnancy test the first day (if applicable); pregnancy and reliable contraception questionnaire at each visit

•The RA will then complete baseline assessments with the patient, as in the table of study assessments (see Table 1).

•The patient will then be taken to a room where the intervention will be delivered by the clinician. Blood pressure and heart rate will be measured by the clinician before and after the stimulation.

•After the 20-min intervention is complete, the patient will be given somewhere to wait, and will be followed up by the RA on a regular basis using the Y-BOCS challenge as well as noting any adverse side effects. A questionnaire developed by Brunoni et al. (2011) designed to record adverse events (AEs) related to tDCS will be used.

•Neurocognitive tests at 3 h

•Four hours after the intervention, the clinician will return to review the patient then deliver the intervention a second time, again for a duration of 20 min.

•The patient will be asked to wait again in the centre, and followed up by the RA for the duration of 2 h using the Y-BOCS challenge, as well as noting any adverse events (AEs).

•The clinician will review the patient before they leave, inclusive of checking the patient’s blood pressure and heart rate.

•The RA will phone the patient to conduct the assessments at 4 h after the second stimulation.

•It is anticipated that the patient will be in the centre for 8 h on the first visit.

#### Second visit (Day 2)

•The clinician will review the patient on arrival; they will then complete assessments as per the table of assessments with an RA (see Table 1).

•The clinician will then deliver the 20-min intervention. Blood pressure and heart rate will be measured by the clinician before and after the stimulation.

•The RA will follow up the patient on a regular basis using the Y-BOCS challenge, as well as noting any AEs.

•Four hours after the intervention, the clinician will return to review the patient and deliver the intervention a second time, again for a duration of 20 min.

•The RA will follow up the patient on a regular basis using the Y-BOCS challenge, as well as noting any AEs.

•The clinician will review the patient before they leave, inclusive of checking the patient’s blood pressure and heart rate.

•The RA will phone the patient to conduct the assessments at 4 h after the second stimulation.

#### Follow-up via telephone

•The RA will follow up with patient via telephone, 24hours, 7 days and 14 days after the second visit. The last study follow up will be 28 days after the final stimulation.

After a 4 week wash-out period, this 2 day cycle will be repeated using a different intervention according to which of the 6 permutations the patient is randomised to receive. Patients will be required to keep their current psychiatric medication dose stable and not to initiate cognitive behaviour therapy during the 12 weeks of the study. This is to avoid any effect of change in treatment being recognised as a change resulting from the treatment provided in the study. Should these restrictions prove unacceptable or a change in treatment is required for a clinical reason the patient will be withdrawn from the study.

### Withdrawal criteria

Willingness to take part in the study will be confirmed with the patient at the beginning of each round of stimulation (i.e. on Day 1), the patient may withdraw from the study at any point. The research clinician will also check that the patient remains eligible for the study for the duration of the time that they are a participant. Should a patient become ineligible, they will be withdrawn from the study. Furthermore, if a patient reports any serious adverse experiences, they will be withdrawn from the study.

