### Measures

#### Baseline data

The following assessments will be used to gather baseline data (all outlined in Table 1).Yale-Brown Obsessive–Compulsive Scale (Y-BOCS) [44]Yale-Brown Obsessive–Compulsive Challenge Scale (Y-BOCCS Challenge): challenge version of the Y-BOCS (10), which is designed for researchers or patients to evaluate short-lived changes in symptom severity using a visual analogue scale [45]Clinical Global Impressions Scale (CGI-S) [46]Montgomery-Åsberg Depression Rating Scale (MÅDRS) [47]Barratt Impulsiveness Scale (BIS) [48]Sheehan Disability Scale (SDS) [49]Neurocognitive tests: CANTAB (Stop Signal Reaction Time Test, Intra-Extradimensional Set Shift), Prisoner’s Dilemma test (cooperation test). The Fabulous Fruit game (habit learning test): only patients who have attended a screening appointment in person prior to the 13th March 2020 (when research activity was paused due to COVID-19) will be assessed using the Fabulous Fruits Game on stimulation days. Patients who are screened over the phone, will not be familiarised with the Fabulous Fruits Game (as it is not possible to do this remotely) and therefore will not be assessed using the Fabulous Fruits Game on stimulation days.

**Table 1 Tab1:** Table of study assessments

Conducted By	Test	Screening (completed by Clinician)	In centre assessments for each of 3 sessions (Sham, OFC, SMA) Day 1										In centre assessments for each of 3 sessions (Sham, OFC, SMA) Day 2									Follow-up via telephone^b^		
			Baseline	Intervention	1 h	2 h	3 h	4 h	Intervention	1 h	2 h	4 h	0 h	Intervention	1 h	2 h	4 h	Intervention	1 h	2 h	4 h	24 h	7 days	14 days
DR	DSM-5	X																						
DR/RA	Y-BOCS	X	X										X									X	X	X
DR/RA	Y-BOCS Challenge		X		X	X		X		X	X	X	X		X	X	X		X	X	X	X	X	X
RA	CGIS		X										X									X	X	X
DR/RA	MÅDRS	X	X																			X	X	X
RA	BIS		X																					
RA	SDS		X																			X	X	X
RA	CANTAB		X				X																	
RA ^a^	AEs		X		X	X		X		X	X	X			X	X	X		X	X	X	X	X	X
DR	Clinical Review		X					X			X		X				X			X				
	**Time (min)**	**60**	**105**	**20**	**15**	**15**	**30**	**30**	**20**	**15**	**15**	**30**	**30**	**20**	**15**	**15**	**20**	**20**	**15**	**15**	**30**	**15**	**15**	**15**

^a^The RA will complete the AE questionnaire with participants and refer to the clinician if necessary

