^b^There will be an additional telephone call at 28 days only after the patients have completed the last arm of the intervention. The assessments will be the same as the previous phone calls (prior to this, day 28 will be day 1 of the next intervention arm that the patient completes)

Adverse events will be recorded using a questionnaire developed by Brunoni et al. [50] developed specially for tDCS. This asks patients to rate 10 symptoms on a scale of 1–4 (see Table 2).

**Table 2 Tab2:** tDCS Adverse Effects Questionnaire

tDCS Adverse Effects Questionnaire – Session ____________________			
Do you experience any of the following symptoms or side effects?	Enter a value (1–4) in the space below (1, absent; 2, mild; 3, moderate; 4, severe)	If present: Is this related to tDCS? (1, none; 2, remote; 3, possible; 4, probable; 5, definite)	Notes
Headache Neck pain Scalp pain Tingling Itching Burning sensation Skin redness Sleepiness Trouble concentrating Acute mood change Others (specify)			

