### End of trial

The end of the trial will be defined as the date that the last patient has their 28-day follow-up and clinical review from the third round of the intervention. In order to assess compliance in patients receiving tDCS, at each of the follow-up visits, the research psychiatrist will record in the CRF information on attendance at scheduled stimulation sessions, length of sessions and the completion of the study assessments. The research psychiatrist formally assesses the patient’s tolerability, clinical status and willingness to continue and records this in the CRF.

If a patient is not attending the stimulation sessions, the clinician will attempt to contact, ascertain the reason from the patient and record in the CRF. The patient will be encouraged to continue to attend the planned stimulation sessions; however, if the patient no longer wishes to receive tDCS, they will be asked if they will still continue to be assessed by the research assistant. If they do not wish to continue with tDCS, the withdrawal from study treatment form will be completed in the CRF.

At the end of the trial, the patient will be referred by the research psychiatrist to the relevant mental health services for further assessment and treatment.

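### Patients withdrawn for a serious adverse experience or lost eligibility are not offered the remaining ratings of the current course, while patients who choose to stop tDCS are (minor)

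*Protocol article*

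**What the plan says.** Withdrawal criteria gives two rules that take the patient out of the study altogether. One covers harm: "if a patient reports any serious adverse experiences, they will be withdrawn from the study". It has no condition that the event be related to tDCS. The other covers eligibility: "Should a patient become ineligible, they will be withdrawn from the study".

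End of trial describes another route. For a patient who stops attending and declines further stimulation, "if the patient no longer wishes to receive tDCS, they will be asked if they will still continue to be assessed", and "the withdrawal from study treatment form will be completed in the CRF". So the protocol knows the difference between leaving treatment and leaving the study, but ties continued rating to the patient's own choice.

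Follow-up via telephone adds a third trigger in the same terms: if "a change in treatment is required for a clinical reason the patient will be withdrawn from the study". Here the protocol gives its reason: "This is to avoid any effect of change in treatment being recognised as a change resulting from the treatment provided in the study".

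The ratings at issue are in Table 1. Each call at 24 h, 7 days and 14 days carries Y-BOCS, Y-BOCS Challenge, CGIS, MÅDRS, SDS and the adverse-event questionnaire. A 28-day call with the same content is made only after the last course; in the earlier courses, "prior to this, day 28 will be day 1 of the next intervention arm that the patient completes".

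**The concern.** A patient who simply prefers to stop is invited to go on being rated. A patient stopped because of a serious adverse experience is not, although that patient's later course is of more interest. Some routes to ineligibility also reflect worsening: the exclusion for a clinician's judgement of significant self-harm risk (Participants) is the clearest. For these patients the missing ratings would be related to the outcome.

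Two uses of the data are exposed. Safety is among the primary objectives, and the structured adverse-event questionnaire and MÅDRS would end early in the very course in which the patient was harmed or worsened. Duration of effect relies on the 7- and 14-day Y-BOCS to find when scores return to their level before stimulation; those ratings would be missing more often in patients who did badly. Recording the reason for a missing rating, as planned under Adherence to tDCS and study assessments and under Data management, identifies the gap but does not fill it.

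**Working it through.** The plan states no figure for such withdrawals, so there is none to reproduce. The check has two parts.

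**1. Does any other section restore the ratings?**

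- Long-term follow-up assessments sets out the 7-, 14- and 28-day schedule, but as the ordinary path to the next stimulation cycle. It says nothing about withdrawn patients. It does keep clinician telephone follow-up of reported adverse events.
- Qualitative assessments offers an exit interview to patients who opt to discontinue. It is qualitative and again depends on patient choice.
- Acceptability, tolerability and safety keeps incident logging in the weeks after exposure. Trial monitoring and oversight keeps serious adverse event reporting.

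These preserve the event record. None supplies Y-BOCS, MÅDRS, SDS or CGIS ratings after withdrawal.

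**2. How much could be lost?**

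Inputs: 25 patients, three courses, calls as in Table 1. Count days from the second visit (day 0), so the first visit is day −1 and the cycle to day 28 lasts 29 days.

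| Trigger falls between | Days | Calls lost, courses 1 and 2 | Calls lost, course 3 |
|---|---|---|---|
| day −1 and 1 | 2 | 3 | 4 |
| day 1 and 7 | 6 | 2 | 3 |
| day 7 and 14 | 7 | 1 | 2 |
| day 14 and 28 | 14 | 0 | 1 |

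The most a patient can lose is 3 × 6 = 18 instrument ratings, or 4 × 6 = 24 in course 3.

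If the trigger is spread uniformly over the cycle (assumption):

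- Courses 1 and 2: (2×3 + 6×2 + 7×1 + 14×0)/29 = 25/29 = 0.86 of 3 calls.
- By call: 24 h lost in 2/29 = 6.9%, 7-day in 8/29 = 27.6%, 14-day in 15/29 = 51.7%. No call is lost in 14/29 = 48.3%.
- Course 3: (2×4 + 6×3 + 7×2 + 14×1)/29 = 54/29 = 1.86 of 4 calls.
- Trigger equally likely in each course: (25 + 25 + 54)/87 = 104/87 = 1.20 calls.

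Planned calls: 25 × 3 × 3 = 225 at 24 h, 7 and 14 days, or 25 × (3 + 3 + 4) = 250 with the final 28-day call. For an assumed 1 to 5 affected patients:

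- 0.86 to 4.3 of 225 lost (0.4 to 1.9%); at most 3 to 15 (1.3 to 6.7%).
- 1.2 to 6.0 of 250 lost (0.5 to 2.4%).
- 24 h ratings lost: 1 × 2/29 to 5 × 2/29 = 0.07 to 0.34.

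Uniform timing fits the schedule poorly. Table 1 places clinical reviews on Days 1 and 2 only, so loss of eligibility will often come to light on a stimulation day (all remaining calls of that course lost) or at the next course's Day 1 (no call of the preceding course lost). Between these, the route is the rater: "The RA will complete the AE questionnaire with participants and refer to the clinician if necessary". The averages and percentages are therefore illustrative; the range per patient, 0 to 3 calls (0 to 4 in course 3), follows from the schedule itself.

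**The case against.** **The loss is inferred.** Nothing says in words that ratings stop after withdrawal, and the article condenses a full protocol that may say more. That is fair, but the article states both the rule and the condition on the offer of further assessment, and the plain reading of the two together is that these patients leave the schedule.

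**The safety comparison hardly changes.** A reader might infer that harms go unrecorded. The documents do not support this: the triggering event is logged, reported and followed up by a clinician. The McNemar test is paired and binary, so a patient withdrawn for a serious adverse experience already counts as having an event in that condition. Later questionnaires could add only other event types. This objection stands and limits the point.

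**Little would be recovered for between-condition tests.** A patient stopped in course 1 has no second condition to pair with. Nor can the loss of later courses be blamed on this rule: they are lost because stimulation stops. Both stand. What remains is mainly the within-target duration analysis, and only where the stopped course was active.

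**The progression criterion might seem threatened.** If 1 to 4 of 25 patients, each worse by 0.5 to 1.0 SD, all lost their 24 h rating in an active course and the rest averaged a 0.30 SD benefit, the observed effect would be too high by about 0.03 to 0.21 SD, against a lower-limit target of 0.1. That stronger reading is not supported, because the 24 h call is lost only when the trigger precedes it.

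**Ineligibility need not mean worsening.** Pregnancy, a scalp lesion, physical illness or joining another treatment study would also count, and the MÅDRS limit of 30 is defined at baseline. This stands: selectivity applies to harm and to some eligibility losses, not to all.

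**Ratings after a treatment change are confounded.** Patients at risk of self-harm will often need such a change, so part of what is recovered could not enter the main duration analysis. This is conceded and handled in the fix; the ratings keep their value for safety.

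**Conclusion.** The point holds as a minor one. The withdrawal wording removes from rating the patients stopped for harm and those whose ineligibility reflects worsening, while patients who merely decline tDCS are offered continued rating. The case rests on which patients lose ratings, not on how many ratings are lost. The main loss is later structured adverse-event and MÅDRS follow-up in the current course, and the 7- and 14-day ratings behind the duration-of-effect analysis. Any-event status in the safety comparison and the 24 h effect size are little affected.

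The frequency is unknown: the article gives no withdrawal rate and expects few adverse events. The percentages rest on an assumed 1 to 5 affected patients and an assumed timing of triggers, and should not be read as forecasts. The treatment-change rule is a weaker case, since the protocol gives a sound reason for it.

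**What to change.** In Withdrawal criteria, replace withdrawal from the study by withdrawal from study treatment for the two triggers there: serious adverse experience and lost eligibility. When to stop stimulation stays a clinical decision. Extend the End of trial offer of continued rater assessment to these patients, with consent, for the calls already scheduled in the current course.

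Where medication has changed or CBT has begun, whether the patient leaves under the treatment-change rule or through lost eligibility, offer the same calls. Flag ratings taken after the change, keep them out of the main duration-of-effect analysis, and use them for safety and sensitivity analysis only.

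The cost is a change of wording plus, per affected patient, at most 3 × 15 = 45 minutes of rater time, or 4 × 15 = 60 minutes in the last course (taking the 28-day call to be as long as the others, since its content is the same). No contact is added beyond those already planned.

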### End of trial

The end of the trial will be defined as the date that the last patient has their 28-day follow-up and clinical review from the third round of the intervention. In order to assess compliance in patients receiving tDCS, at each of the follow-up visits, the research psychiatrist will record in the CRF information on attendance at scheduled stimulation sessions, length of sessions and the completion of the study assessments. The research psychiatrist formally assesses the patient’s tolerability, clinical status and willingness to continue and records this in the CRF.

If a patient is not attending the stimulation sessions, the clinician will attempt to contact, ascertain the reason from the patient and record in the CRF. The patient will be encouraged to continue to attend the planned stimulation sessions; however, if the patient no longer wishes to receive tDCS, they will be asked if they will still continue to be assessed by the research assistant. If they do not wish to continue with tDCS, the withdrawal from study treatment form will be completed in the CRF.

At the end of the trial, the patient will be referred by the research psychiatrist to the relevant mental health services for further assessment and treatment.

### Sample size calculation

Study sample size is evaluated with respect to the primary outcome (difference in the challenge Y-BOCS between tDCS and Sham), given that the aim is to estimate the likely effect size of a future trial. We assume that the sample will be representative of the population, and that the observed variance, and Y-BOCS scores in each condition will allow for estimation of a typical group comparison. Given that there are only 4 exposures of tDCS in each study condition, with 4 weeks between exposures, we assume no carry-over effects, which will be tested using a mixed model. Each tDCS target (OFC and SMA) will be considered independently against Sham. Published estimates of effect size vary widely [45]; thus, a conservative estimate of *d* = .3 is assumed. Following Cocks and Torgersen [51], assuming *α* = 0.05, 1 – *β* = 0.80, a sample size of 20 per group allows detection of a lower limit of *d*’ > 0.1 for an expected effect size *d*’ = 0.3. An additional 5 patients will allow for a 25% dropout.

It is estimated that approximately 25 patients will be recruited from a pool of 200 patients identified from screening, giving power to estimate the ascertainment ratio to within ± 6%. The proportion of missed treatment sessions is expected to be less than 20% from a total of 206 sessions, giving a precision within ± 6%. At the outset of the study, it is not possible to estimate the likely number of reported adverse events (safety), which is expected to be low, and cannot therefore estimate the likely precision of estimation.

Time-dependent changes in the Y-BOCS scores, and in the CANTAB test scores will be considered using standard paired comparisons (*t* test). A sample size of *N* = 20 allows for detection of an effect size *d*’ = .65 with power 1 – *β* = .78, and an effect size *d*’ = .77 with power 1 – *β* = .90. A time-dependent model will be evaluated (mixed model) to examine trends over time, but with limited power.

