### Design

This feasibility study is designed as a double-blinded, sham-controlled, crossover randomised multicentre design in adults with OCD.

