##### Likely effect size

The primary focus on comparisons will be on the potential effect size at 24 h after the final stimulation in each treatment condition. The observed and the lower limit for the effect size for the OFC and SMA targets will be evaluated with respect to the Sham condition, assuming that no carryover effects are observed in the crossover design (mixed model). A lower limit for effect size of < 0.1 will indicate a positive signal to proceed. Where possible, treatment target differences will be adjusted in a mixed model to account for baseline values of key patient variables.

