### Progression to a full trial

The decision whether to progress will be based on consideration of all findings, but principally on the following data:The acceptability of tDCS will be considered throughout the ascertainment ratio (target 10%), willingness of clinicians to recruit to the study, and the numbers of patients citing tDCS as the reason for refusal (< 20%).Feasibility of recruiting sufficient patients in a multicentre national study will be evaluated in relation to the population size in each of the study centres, and extrapolation to the number of centres required to achieve the required sample size for a full-scale trial.The study targets a lower limit for the effect size of tDCS > .1, giving confidence that the effect of tDCS is at least .3. The study will enable evaluation of the superiority of the two tDCS target sites (OFC or SMA, given limited power).Differences between the targets will be considered in the light of differences in the profile of the neurocognitive tests indicating that the changes are consistent with the hypothesised effects (SMA target: motor impulsivity; OFC target: cognitive flexibility, cooperation).

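### The sample size statement (α = 0.05, power 0.80, lower limit above 0.1 at d = 0.3) does not follow for a paired crossover with 20 completers

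*Protocol article*

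**What the plan says.** The design is a "double-blinded, sham-controlled, crossover randomised multicentre design", so each patient is compared with himself or herself. For the effect of tDCS, the Sample size calculation says that "a conservative estimate of *d* = .3 is assumed". It then continues, "assuming *α* = 0.05, 1 – *β* = 0.80", that "a sample size of 20 per group allows detection of a lower limit of" a standardised effect greater than 0.1. Five more patients are added for dropout. The same section adds that "Each tDCS target (OFC and SMA) will be considered independently against Sham" and that the observed variance and scores "will allow for estimation of a typical group comparison". It gives no confidence level, sidedness, within-patient correlation or SD for scaling d.

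The limit is used twice more. Progression to a full trial lists it among the principal data for the decision: "The study targets a lower limit for the effect size of tDCS > .1". The Likely effect size section writes the inequality the other way round: "A lower limit for effect size of < 0.1 will indicate a positive signal to proceed".

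**The concern.** The sentence joins an error rate, a power, a sample size, an expected effect and a lower limit. For within-patient data at n = 20 these do not appear to fit together. A 95% limit around 0.3 should lie well below 0.1, and a criterion whose expected value sits only just above its threshold is met about half the time, not 80% of the time.

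At stake is how the effect-size result is read. The study is sized on this sentence, and Progression to a full trial uses the same threshold. Someone relying on the stated 0.05 and 0.80 would misjudge both how often the criterion is met by chance and how often it is missed when the assumed effect is real.

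**Working it through.** **Inputs.** From the Sample size calculation: n = 20 completers, expected d = 0.3, threshold 0.1, α = 0.05 (sidedness not given), 1 − β = 0.80. From Design: crossover. Normal quantiles: z = 0.842 (one-sided 80%), 1.645 (one-sided 95%), 1.960 (two-sided 95%).

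**1. The section's own paired t-test figures reproduce.** For a two-sided test at α = 0.05 with 19 degrees of freedom, the noncentrality is d√20.
- d = 0.65: 0.65 × 4.472 = 2.907, power 0.787 (article: .78).
- d = 0.77: 0.77 × 4.472 = 3.444, power 0.904 (article: .90).
- The same test at d = 0.3: 0.3 × 4.472 = 1.342, power 0.25.

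So at α = 0.05, 20 pairs are powered for an effect of about 0.65, not 0.3.

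**2. Expected lower limit, d in SDs of the paired difference.** SE = 1/√20 = 0.2236; limit = 0.3 − z × SE.
- One-sided 80%: 0.3 − 0.842 × 0.2236 = 0.11
- One-sided 95%: 0.3 − 1.645 × 0.2236 = −0.07
- Two-sided 95%: 0.3 − 1.960 × 0.2236 = −0.14

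Exact noncentral-t limits are 0.10 (0.104), −0.08 and −0.15, so the normal approximation does not drive the result.

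**3. Probability that the limit exceeds 0.1.** The observed d must exceed c = 0.1 + z × SE, and P = 1 − Φ((c − d)/SE).

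| Limit | c | true d = 0 | d = 0.1 | d = 0.3 |
|---|---|---|---|---|
| One-sided 80% | 0.288 | 0.10 | 0.20 | 0.52 |
| One-sided 95% | 0.468 | 0.02 | 0.05 | 0.23 |
| Two-sided 95% | 0.538 | 0.01 | 0.025 | 0.14 |

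Simulation of 200,000 trials per scenario, using t limits, gave 0.520, 0.224 and 0.142 at d = 0.3. No row combines a 5% error with 80% power. Taken literally, a one-sided 5% test against 0.1 with 80% power at 0.3 needs ((1.645 + 0.842)/0.2)² = 154.6, that is 155 completers.

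**4. If d is scaled by the between-patient SD.** Then SE = √(2(1 − ρ)/20), with ρ the within-patient correlation. An expected limit above 0.1 needs z × SE < 0.2, that is ρ > 1 − 10 × (0.2/z)².
- One-sided 80%: ρ > 0.435, about 0.44
- One-sided 95%: ρ > 0.852, about 0.85
- Two-sided 95%: ρ > 0.896, about 0.90

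The article gives no ρ, so these are thresholds for an assumption and not estimates.

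**The case against.** The strongest reply is that the pair of 20 patients and a limit above 0.1 can be recovered: a one-sided 80% limit on the paired scale gives 0.11. This may be what the authors computed, following a source that is not available here. In that case the sample size stands and only the labels are wrong. That is largely right, and it is why the remedy does not touch n. It does not rescue the sentence, because the article does not state that limit and the stated 0.05 and 0.80 fail under it too.

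Several stronger readings are tempting but not supported:
- *The 0.80 is really a confidence level.* A reader might infer this, but it is a reconstruction. The figures could also have been meant for the future trial; the text does not settle it.
- *Per group means two parallel groups of 20.* Design, the Randomisation scheme and the paired analyses all fix a crossover. The phrase is loose wording, so parallel-group limits are not a fair test.
- *The limit is a stand-alone go rule, with an overall error across the two targets.* Progression to a full trial weighs all findings, including acceptability, recruitment and the neurocognitive profile. It does not say that one target alone triggers progression or that a missed limit stops it.
- *More patients are needed.* The 155 above shows only what the stated error rates would imply. The Statistical analysis section calls the feasibility analysis descriptive and the sample limited.

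It is also fair that a chance near one half is unsurprising when a limit is quoted at the expected effect. The article, however, attaches 0.80 to it.

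**Conclusion.** The concern holds as a misstated precision. With 20 completers, paired data and d in SDs of the difference, α = 0.05 puts the expected lower limit at −0.07 or −0.14, not above 0.1. The only limit examined that reaches 0.1 on this scale is an unstated one-sided 80% limit. Under it the criterion is met 52% of the time at d = 0.3 and 10% of the time per target at d = 0. With 95% limits it would be met 23% (one-sided) or 14% (two-sided) of the time at d = 0.3. So at the assumed effect the criterion would be missed in about 48% to 86% of trials, depending on a limit the article leaves open.

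This rests on 20 completers per contrast, roughly normal differences, no carry-over, and the above-0.1 direction used in two of the three places. On the between-patient scale the claim could hold, but only with an assumed correlation of about 0.44 or more (one-sided 80%) or 0.85 or more (one-sided 95%). Because the limit is one of several progression inputs and the affected analysis is secondary, this is a should-fix.

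**What to change.** Keep n. In the Sample size calculation, delete the α and 1 − β values and the per-group wording from the sentence on the lower limit. State the confidence level, sidedness and scale of d actually used, with the assumed correlation if d is on the between-patient SD. Then give the matching expected limit and the probability of meeting the criterion. If the authors confirm a one-sided 80% limit on the paired scale, the text could read: *Twenty completers give an expected one-sided 80% lower limit of about 0.11 for a true d of 0.3, in SDs of the paired difference; the chance that the limit exceeds 0.1 is about 52% at d = 0.3 and 10% per target at d = 0.*

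Use that same limit in Likely effect size and in Progression to a full trial, and change the inequality in Likely effect size from below 0.1 to above 0.1 so that all three places agree.

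The cost is rewording only, with no extra patients or visits. The downside is that the stated properties become less favourable.
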